**Methods:**

This study uses a phased cluster randomized mixed method design to test nurse-led implementation of an SBIRT toolkit on one medical-surgical unit at 14 acute care hospitals (critical access, community and academic health centers). Medical surgical units will be randomly assigned to implement the SBIRT toolkit (engagement and communication, assessment, planning, training, and evaluation tools) or a wait-list usual care control group that begins implementation 6 months later. Primary endpoints are documentation of SBIRT delivery in randomly selected electronic medical records at baseline, 6 months and 12 months after group 1 implementation (61 records per unit per time period, N = 2562). Two surveys will be administered to unit nurses: smoking cessation activities will be assessed at baseline and SBIRT use will be assessed on randomly-selected days after implementation. In addition, site coordinators will complete a baseline capacity assessment, an implementation fidelity survey post-implementation, and a structured interview at the end of the study. Multilevel mixed-effects effects logistic and linear models will be used to analyze use of SBIRT and cost outcomes.

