### Statistical analysis

A sample size calculation was conducted to determine the number of medical records needed in each of the 14 study hospitals, to achieve an 80% power at an alpha level of 0.05 to address the quantitative aims of the study while taking the clustered randomization into consideration [61, 62]. Sample size calculations were based on an intracluster correlation of 0.03. In case intracluster correlation is lower than 0.03, our statistical tests provide an even larger statistical power. For the between-group comparisons regarding the binary outcomes of Aim 1, detecting an absolute difference in a proportion between the two groups of 16% with an at least 80% power, using a Z-statistic that accounts for the intracluster correlation, requires 61 medical records per hospital. Based on this sample size for each observation time-point, we are also sufficiently powered to test for within group changes in the control group (post-intervention vs pre-intervention) since within-group comparisons are expected to have a larger power compared to between-group comparisons. Sample size calculations were conducted using the PASS 13 software.

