Evaluation of the effect of implementation strategies will be focused on the use of SBIRT. To estimate the effect of implementation (training, toolkit) of SBIRT on clinical processes, we will use multilevel mixed-effects logistic regression models to account for both the hospital unit clustering effects and the potential observation dependence within each phase of the study (i.e., baseline, 6 months, 12 months), while adjusting for variables found to be imbalanced between the study groups. Potential confounders such as organizational and nurse attributes will also be considered for inclusion in the model to avoid any residual confounding effects. Based on these models, both between and within-group effects will be estimated and model-based estimates of the effect size (i.e., odds ratio) will be calculated along with the associated 95% confidence intervals. We will additionally evaluate the intervention effect sustainability in the intervention group by comparing, using the appropriate estimate from the fitted model, the proportion of SBIRT use at 6 months versus the corresponding use at 12 months.

#### Aim 2

Evaluation of the cost of implementation and delivery of SBIRT will be focused on the system perspective. Tailored implementation of SBIRT for local healthcare settings requires appropriate budgeting and resources. Data on both human resources and tangible resource use will be measured during the current study. These data will inform future implementation and budgeting. We will estimate costs of implementation based upon phase of implementation, including the start-up, deployment, and maintenance costs of the adoption of SBIRT. Specific cost categories will collected via the monthly worksheet including personnel (training & education; deployment), site coordinator time spent on implementation, and SBIRT related expenses (e.g., written materials). Costs of SBIRT delivery will be estimated using a random sample of registered nurse’s report of estimated minutes interacting with the patient during the SBIRT process. The cost outcomes will be analyzed using mixed-effects linear regression models to account for the hospital unit clustering.

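### Aim 1 does not fix the between-group contrast and adjusts only for observed imbalance, so use of each unit's baseline documentation rate depends on the realised data

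*Protocol article*

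**What the plan says.** The Abstract (Methods) defines the primary endpoints as "documentation of SBIRT delivery in randomly selected electronic medical records at baseline, 6 months and 12 months after group 1 implementation", with 61 records per unit per period and 2562 in all. Under Study design and sample, seven hospitals start first and seven start 6 months later, so 6 months is the time-point at which toolkit and usual care are compared before the control group crosses over.

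The Statistical analysis section sizes the between-group comparison for a gap of 16 percentage points, and describes the calculation as one "using a Z-statistic that accounts for the intracluster correlation, requires 61 medical records per hospital". The inputs are also given there: "Sample size calculations were based on an intracluster correlation of 0.03", 80% power and alpha 0.05. No baseline term enters that calculation.

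The analysis itself is wider than the sizing. Aim 1 specifies a multilevel mixed-effects logistic model that covers unit clustering and all three phases, baseline included. It continues: "Based on these models, both between and within-group effects will be estimated". It does not say whether the between-group effect is the 6-month difference, the difference in change from baseline, or a baseline-adjusted difference. On covariates, the general text and Aim 1 both promise adjustment for variables that prove unbalanced between the groups. Aim 1 adds that organisational and nurse attributes may be considered. The unit's baseline documentation rate is not named.

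**The concern.** With 14 units, variation between units drives much of the error of the main comparison, and a unit's own baseline rate on the same endpoint is the natural predictor of its later rate. A third of the abstraction effort (14 x 61 = 854 of 2562 records) goes into measuring it.

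The only adjustment rule stated that could bring it into the model is triggered by what the data show. In one realisation of the trial the baseline rate would be adjusted for, and in another it would not. The choice among three contrasts with quite different precision would also remain open once results are visible. At stake are the width of the confidence interval for toolkit v usual care, and how the result is read when 7 v 7 units happen to start at different levels.

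**Working it through.** **Inputs from the Statistical analysis and Study design sections.** 7 units per arm, m = 61 records per unit per period, ICC 0.03, difference 0.16, alpha 0.05 (taken as two-sided), power 80%.

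**Assumed, because the article gives no figure.** Proportions of 42% v 58%, which is the worst case for a 16-point difference. Cluster autocorrelation (CAC: the correlation of a unit's underlying rate between periods) of 0.5 to 1.0.

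**1. The plan's own figure.**
- Effective records per arm, pooled-variance Z formula: n = [1.96 x sqrt(2 x 0.5 x 0.5) + 0.8416 x sqrt(0.42 x 0.58 + 0.58 x 0.42)]² / 0.16² = 152.1.
- Solving 7m / [1 + (m - 1) x 0.03] = n gives m = n x 0.97 / (7 - 0.03n) = 60.6, which rounds up to 61.
- The stated 61 reproduces as a two-group comparison at one time-point with no baseline term.

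**2. Precision of the 6-month difference alone.**
- Design effect = 1 + 60 x 0.03 = 2.8.
- SE = sqrt[(0.42 x 0.58 + 0.58 x 0.42) x 2.8 / (7 x 61)] = sqrt(0.4872 x 2.8 / 427) = 0.0565.
- Z power = Phi(0.16 / 0.0565 - 1.96) = 80.8%.

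**3. Correlation of a unit's observed baseline and 6-month rates.** r = CAC x (61 x 0.03) / 2.8 = 0.654 x CAC.

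**4. Variance of each contrast relative to the 6-month difference, with Z power.** Change from baseline has relative variance 2(1 - r). Conditioning on baseline, by covariate or by a common baseline mean, has 1 - r².

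| CAC | r | 6-month only | Change from baseline | Baseline-adjusted |
|---|---|---|---|---|
| 0.5 | 0.33 | 1.00, 81% | 1.35, 68% | 0.89, 85% |
| 0.8 | 0.52 | 1.00, 81% | 0.95, 83% | 0.73, 91% |
| 1.0 | 0.65 | 1.00, 81% | 0.69, 92-93% | 0.57, 96% |

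Generalised least squares on the unit-by-period means (a linear approximation to the logistic model) gives the same relative variances. With free group means at each phase, the 6-month contrast stays at 1.00 although the baseline rows are in the dataset.

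**5. Small-sample check.** Z is optimistic with 14 units. In unit-level simulation (6000 runs per scenario, t tests on 12 df unadjusted and 11 df with a baseline covariate), power for 6-month only v adjusted is 73% v 73% at CAC 0.5, 73% v 81% at 0.8 and 72% v 88% at 1.0. At CAC 0.3 the covariate form loses about 3 points in a t-based approximation.

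**6. Chance baseline gap between arms.** At 50% documentation, SD = sqrt(2 x 0.25 x 2.8 / 427) = 5.7 points, a 95% range of about +/-11 points, against the 16-point target. At 10% documentation the SD is 3.4 points.

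**The case against.** Four points can be made for the plan.

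- **The analysis is not a one-time-point comparison.** A reader might infer from the sample size paragraph that the between-group effect is analysed at 6 months alone. The document does not support that: Aim 1 names a model over all three phases. Its fixed effects are not given, and one with phase effects, a time-varying implementation indicator and random unit effects would fit the wording and come close to the fix below. This stands. The claim can only be that the contrast is open.
- **Chance gaps need not stay in the estimate.** A reader might infer that they do. But the imbalance rule could bring in the baseline rate, and a change-from-baseline contrast subtracts the gap. This also stands. What remains is that the first route depends on the data and the second adds baseline noise.
- **An article leaves model terms to the full protocol or SAP.** That is true of a missing contrast taken alone. It is a weaker answer to the adjustment rule, which the article does state and which prespecified conditioning improves on.
- **The gain rests on assumptions.** CAC is not in the document. Sites decide how many nurses to train and design their own referral process, which could weaken the link between baseline and 6 months in intervention units. The Background and Discussion also make low baseline rates plausible. At 5% v 21% the unadjusted Z power is already 99%, so there is little left to gain. This limits the size of the point and not its direction.

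**Conclusion.** The point holds as a weakness in how Aim 1 is fixed. The article leaves the between-group contrast open and ties adjustment to observed imbalance, so use of the unit's baseline rate is not settled in advance. Of the natural contrasts with free group means, one ignores the baseline records and the other can fall well below the stated power (68% at CAC 0.5). Conditioning on baseline has the smallest variance of the three across the CAC range examined, before the small degrees-of-freedom cost of the covariate form.

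On the Z basis at 42% v 58%, the gain over 6 months alone is about 4, 10 and 15 points of power at CAC 0.5, 0.8 and 1.0. On a t basis with the covariate it is nil at 0.5 and about 8 points at 0.8. It is small or nil at low autocorrelation or very low documentation rates, and nil for an outcome with no baseline documentation, a possibility the Discussion raises for anything beyond initial screening.

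Two further inferences are not supported. A 6-month-only estimate is not biased: it is unbiased over randomisation, and the loss is in precision and in conditional imbalance on 7 v 7 units. Nor is 61 records per hospital wrong: it reproduces, and leaving baseline out of the sizing is conservative for a baseline-adjusted analysis. The change is worth making, with medium confidence in its size.

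**What to change.** In Aim 1, state that the primary between-group effect is the 6-month effect, adjusted for baseline regardless of observed imbalance.

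- **Preferred form.** Constrain the two groups to a common baseline mean in the three-phase mixed logistic model: phase terms plus group-by-post-baseline-phase terms, no group term at baseline, and random unit and unit-by-phase effects.
- **Alternative.** Fit the 6-month records with the unit's baseline documentation proportion as a fixed covariate.
- **Exception.** Omit the baseline term for any outcome with essentially no baseline documentation, and say so in advance.

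The cost is wording only, because the baseline records are already to be abstracted. The covariate form spends one unit-level degree of freedom, which cancels the gain at CAC of about 0.5 and costs a few points of power below that. The common-baseline form avoids most of this.

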### Description of intervention

This study protocol will incorporate standardized education on SBIRT through a train-the-trainer approach. Registered Nurse site coordinators from each hospital will receive 8 h of training on the SBIRT process, system strategies to facilitate organizational uptake, and how to teach SBIRT to others. Study investigators will develop this training. The training will be informed by information from the Substance Abuse and Mental Health Services Administration’s public health model of universal screening, early intervention, and treatment for people who have problematic or hazardous alcohol, drug, or tobacco use and dependence, as well as content from the Indiana Prevention Resource Center and Institute for Research on Addictive Behavior. After the site coordinator training is complete, site coordinators at each facility will train additional clinical nurses in SBIRT and develop a referral process specific to their organization’s needs and resources. The site coordinators may also partner with additional staff within their hospital, including social workers and respiratory therapists, to encourage widespread adoption. The site coordinators will partner with unit leaders at each facility to decide how many additional clinical nurses will receive SBIRT training and which employees will receive training. These training interventions are reproducible, publically available, and do not require direct control from the research team. During training, the site coordinators will receive a toolkit that includes the standardized education, engagement and communication tools, assessment tools, planning tools, and evaluation tools to assist with implementation at their facility.

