To assess adoption and assimilation at the completion of SBIRT training, site coordinators and direct care nurses will complete a 10-item test constructed for this study to assess knowledge about screening tools, motivational strategies, and referral tools. In addition, competency will be assessed using the Brief Intervention Adherence and Competence Scale [56]. These data will be used to evaluate training and verify SBIRT knowledge and competency.

Actual implementation will be assessed using several strategies. Each month, site coordinators will complete a qualitative and quantitative monthly worksheet developed by the investigators that includes information about the time spent on implementation, changes in care processes, barriers and facilitators to implementation, and lessons learned. On five randomly selected days, site coordinators will collect quantitative data regarding SBIRT use. After each patient admission on the randomly selected days, the direct care nurse or site coordinator will complete a survey regarding fidelity to the different components of SBIRT and the time required to complete SBIRT for that patient. Site coordinators will also complete a survey regarding implementation fidelity. This quantitative and qualitative survey includes questions about the number of nurses trained in SBIRT and actions taken to support SBIRT implementation. Finally, all direct care nurses on the study units (including nurses who did not receive training in SBIRT) will be invited to complete the Smoking Cessation Counseling Scale [57–59]. This survey assesses the extent to which clinicians comply with evidence-based smoking cessation guidelines. Data from the monthly worksheets, SBIRT use assessment, implementation fidelity assessment, and smoking cessation counseling scale will be reviewed by the investigators at the completion of data collection. This information will inform feedback to site coordinators, identify barriers and facilitators to implementation, and inform potential modifications to implementation strategies.

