The consequences of SBIRT implementation include the delivery of SBIRT components and the costs of implementation. Delivery of SBIRT components will be measured by the documentation of screening, brief intervention, and referral to treatment for alcohol, drugs, and tobacco, individually and combined. These data will be based on the Joint Commission Quality Measures for alcohol, drug, and tobacco use [60]. The components of SBIRT will be documented in the medical record by healthcare providers who complete the screening, brief intervention, and referral to treatment. All hospitals use the same electronic medical record system. Sixty-one medical records at each site will be randomly selected through automated processes. Inclusion criteria are adult (≥ 18) patients admitted and discharged from units selected for participation in this study within data abstraction periods (baseline, 6 months and 12 months). De-identified data will be abstracted using an electronic data abstraction report. Automated data abstraction will be validated via comparison of electronic and manual data abstraction in a sub-sample of records at each hospital. If required, the site coordinators will conduct the medical record review manually. We will collect data regarding the number of patients screened for alcohol, tobacco, and drugs using a validated tool, and the percentage of patients who screened positive for each substance and then received a brief intervention and/or referral to treatment. The costs of implementation will be assessed using the monthly worksheets completed by the site coordinators and the SBIRT use reports. Data regarding care delivery and costs of implementation will be assessed. At the completion of the study, site coordinators will complete a semi-structured interview to describe their experiences as well as barriers and facilitators of implementation.

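### Aim 2 bases delivery cost on nurse-reported minutes, so it may understate the system's cost at sites where other staff deliver SBIRT components

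*Protocol article*

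**What the plan says.** **Perspective and source of delivery cost (Statistical analysis, Aim 2).** The perspective is stated first: "Evaluation of the cost of implementation and delivery of SBIRT will be focused on the system perspective". The delivery-cost source follows: "Costs of SBIRT delivery will be estimated using a random sample of registered nurse’s report of estimated minutes interacting with the patient". No other staff group is named as a source of delivery time. The monthly worksheet covers different items: staff cost for training and deployment, site coordinator time, and expenses.

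**Respondents (Data sources, Table 3).** Time estimates for each component are assigned to the group coded SN, which the table's footnote defines as trained nurses.

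**Who may be involved (Description of intervention).** "The site coordinators may also partner with additional staff within their hospital, including social workers and respiratory therapists, to encourage widespread adoption". Site coordinators and unit leaders also "decide how many additional clinical nurses will receive SBIRT training and which employees will receive training". Each site develops its own referral process.

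**Whose delivery the record outcome reflects (Data sources).** "The components of SBIRT will be documented in the medical record by healthcare providers who complete the screening, brief intervention, and referral to treatment".

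**The random-day survey (Data sources).** The bedside nurse or the site coordinator completes it after each admission on the selected days. It asks about "fidelity to the different components of SBIRT and the time required to complete SBIRT for that patient".

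**The concern.** The outcome and the cost may not cover the same activity. The record outcome is open to any healthcare provider who completes and charts a component. The delivery cost, as Aim 2 words it, is built from nurse-reported contact time. If a social worker conducts a referral, the chart can show it as done while no delivery minutes are costed for it.

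From a system perspective, the time of every employee who delivers a component is part of the cost. The article says these data are meant to inform later implementation and budgeting, so a hospital that plans to share the work among professions could be given too low a figure. If sharing differs between hospitals, part of any between-hospital cost difference could come from staffing mix. The planned mixed-effects linear model accounts for clustering by unit, but it cannot restore minutes that were never recorded.

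The point is whose time is counted, not which of the nurse's tasks are counted.

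**Working it through.** The plan states no figure for delivery minutes, wages or delivery cost, so there is nothing of its own to reproduce. Its sample-size calculation concerns Aim 1 and has no bearing here.

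**1. The passages side by side**

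| Place | Whose work or time |
|---|---|
| Aim 2, perspective | The health system |
| Aim 2, delivery cost | Minutes reported by registered nurses |
| Table 3, component times | Trained nurses as respondents |
| Description of intervention | Other professions may be involved; sites decide which employees are trained |
| Data sources, record outcome | The healthcare providers who complete the component |
| Data sources, random-day survey | Nurse or coordinator reports time for that patient; whose time is not stated |

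Nowhere does the article describe collecting delivery minutes from staff other than nurses.

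**2. If only nurses' minutes are costed**

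Let s be the share of delivery time given by non-nurses and r their wage relative to nurses. Neither is in the documents; I assume s from 0 to 50% and r from 0.8 to 1.2.

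Understatement = s·r / [(1 − s) + s·r]

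| s | r = 0.8 | r = 1.0 | r = 1.2 |
|---|---|---|---|
| 0 | 0% | 0% | 0% |
| 10% | 0.08/0.98 = 8.2% | 10% | 0.12/1.02 = 11.8% |
| 25% | 0.20/0.95 = 21.1% | 25% | 0.30/1.05 = 28.6% |
| 50% | 0.40/0.90 = 44.4% | 50% | 0.60/1.10 = 54.5% |

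**3. If colleagues' minutes are included but costed at the nurse wage**

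The broader survey wording allows this. Estimated over true cost is then 1 / [(1 − s) + s·r]. At s = 50% this is 1/0.90 = 1.11 for r = 0.8 and 1/1.10 = 0.91 for r = 1.2. Only the wage error remains, and it can go either way.

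**4. A component-level illustration**

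The Background gives about one-third of inpatients positive and, among positives, 68.8% recommended for brief intervention and 17.2% for referral. I assume 3–5 min for screening (a), 10–15 min for a brief intervention (b) and 10–20 min for a referral (c).

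- Minutes per admission = a + (1/3)(0.688b + 0.172c).
- Lowest: 3 + (1/3)(6.88 + 1.72) = 5.9 min.
- Highest: 5 + (1/3)(10.32 + 3.44) = 9.6 min.

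The uncosted share of minutes is:

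- No delegation: 0%.
- Others deliver 10% of brief interventions and 25% of referrals, with a = 5, b = 10, c = 10: (1/3)(0.688 + 0.43) / 7.87 = 4.7%.
- Others deliver 50% of brief interventions and all referrals, with a = 3, b = 15, c = 20: (1/3)(5.16 + 3.44) / 7.59 = 37.8%.

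This is rough. The one-third figure covers drinking and drug use but not tobacco, and the 14.0% recommended for brief treatment are left out.

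**The case against.** A reader might infer that the delivery cost is definitely too low and that hospital differences in cost will reflect staffing mix. The documents do not support that, for four reasons.

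- Involving other staff is optional, and its stated purpose is adoption, not delivery. The trial is described as nurse-led, and no sentence says that another profession will deliver a brief intervention or referral. This stands: the base case may be no bias. But non-nurse delivery is not excluded, because sites choose which employees are trained and design their own referral process.
- In the Aim 2 sentence the nurse is the reporter, and the survey item in Data sources is framed per patient. A nurse could enter a colleague's time. This also stands as a possibility. However, the respondent may not know a colleague's minutes, or may have completed the form before a later referral contact. Without a role, any minutes that are entered cannot be costed at the right wage.
- Some non-nurse staff cost could enter through the worksheet's deployment category. That is possible, so such work need not be wholly absent from Aim 2. But Aim 2 lists that category with implementation cost and assigns delivery cost to the nurses' report.
- The sentence about the record outcome says who charts a component; it is not an explicit rule crediting other professions. That is fair, but nothing in it confines the outcome to components completed by nurses.

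The survey form is not shown and may already have a role field. Its absence from a condensed article is not the point. The point is that the article positively names nurses as the source of delivery time, in Aim 2 and again in Table 3.

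**Conclusion.** The point holds conditionally. Taken together, Aim 2, Table 3, Description of intervention and Data sources leave the delivery cost open to understatement at sites where non-nurse staff deliver components. The understatement is zero where nurses deliver everything. If only nurses' minutes are costed, it is roughly the non-nurse share of delivery time before wage differences: about 8–12% at a 10% share and 44–55% at a 50% share. Those shares and the wage ratio of 0.8 to 1.2 are assumptions, and the documents do not allow a point estimate. The wording of the survey item does not settle whose minutes are counted. The Aim 1 endpoints are unaffected. This is a low-cost improvement to the costing aim, not a flaw in the trial's main comparison.

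**What to change.** Reconcile Table 3, the survey description in Data sources and the Aim 2 paragraph so that delivery cost covers the time of all staff who deliver a component. On the existing random-day survey, record for each component the job role and the minutes of whoever delivered it. Cost each role at its own wage. If the form already records role, only the article's wording and the costing rule need to change.

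The cost is two further entries per component, a slightly longer form and a wage table. Minutes that a nurse or coordinator reports on a colleague's behalf will be approximate, and the report should say so. The entries need to be in place before the survey days, because minutes by role would be hard to recover afterwards.
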